#### Enhanced upper limb therapy programme

The enhanced upper limb therapy programme aims to match the frequency and duration of the robot-assisted training programme sessions. It has been developed from the upper limb therapy programmes used in the Botulinum Toxin for the Upper Limb after Stroke (BoTULS) trial [27–29] and the Repetitive Arm Functional Tasks after Stroke (RAFTAS) project [30]. Using the principles of person-centred goal-setting and repetitive functional task practice, it aims to drive neuroplasticity and motor recovery after stroke.

Participants receive enhanced upper limb therapy at the hub sites for up to 45 min per day, 3 days per week for 12 weeks, in addition to usual care. A detailed description of the enhanced upper limb therapy programme using the TIDieR Checklist [26] is provided in Table 1.

#### Usual care

Defining usual care is a challenge for any stroke rehabilitation trial. One of the current NICE quality standards is that ‘patients with stroke should be offered a minimum of 45 min of each appropriate therapy that is required, for a minimum of 5 days a week, at a level that enables the patient to meet their rehabilitation goals for as long as they are continuing to benefit from therapy and as long as they are able to tolerate it’ [31]. For most stroke services this is aspirational and the majority of patients do not receive this intensity particularly after discharge from hospital or early supported discharge services [32]. Patients with chronic stroke are unlikely to receive ongoing rehabilitation in the longer term. Most services do not regularly review patients to address unmet rehabilitation needs beyond 1 year.

Usual care is delivered at hub and spoke sites.

Participants in all three randomisation groups receive a study ‘arm rehabilitation therapy log’ where they are asked to record any ‘usual’ upper limb rehabilitation that they receive during the course of the study. Periodic text message reminders are sent to remind participants about completion of the rehabilitation logs. In addition, participants in all three randomisation groups receive regular study newsletters.

### Outcome assessments

Outcomes are assessed at 3 months (±7 days) and 6 months (±7 days) following randomisation.

Assessments are undertaken in two stages:

Stage 1 is a self-completion postal questionnaire consisting of the Stroke Impact Scale (SIS) [33] (3 and 6 months) and the adapted Client Services Receipt Inventory resource utilisation questions (6 months only) [20–22].

Stage 2 is a face-to-face assessment with a researcher blinded to randomisation group. The following data are collected: Barthel ADL Index [16, 17], EQ-5D-5L [18], ARAT [11], Fugl-Meyer Test (motor and sensory arm sections [15]), and adverse events. At the end of the 6-month stage-2 assessment, participants are given a further self-completion questionnaire and are asked to return this by post. This questionnaire contains time and travel resource use questions [34, 35].

### Blinding

Due to the nature of the interventions, it is not possible to blind participants or treating therapists to treatment allocation. It is intended that stage-2 outcome assessments are conducted by a researcher blinded to treatment allocation. After each outcome assessment the researcher is asked to record whether they have unintentionally become aware of treatment allocation due to conversation with the participant. Success of outcome assessment blinding will be reported.

### Study withdrawal

No specific withdrawal criteria have been pre-set. Participants may withdraw from the study at any time for any reason. Data collected prior to withdrawal will be used in the study analysis unless consent for this is specifically withdrawn. Should a decision to withdraw from the study be made, a reason for withdrawal is sought but participants can chose to withdraw without providing an explanation.

Investigators, GPs, stroke physicians and therapists may also withdraw participants from the study at any time if they feel it is no longer in their interest to continue; for example, because of intercurrent illness or adverse events.

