### Statistical analysis

#### Primary analysis

The primary outcome is arm function measured by the ARAT [11] at 3 months. It has been suggested that the minimal clinically important difference for the ARAT is 10% of its range (6 points) [37] but a smaller treatment effect may be clinically beneficial in those with severe initial upper limb functional limitation who are likely to improve less than those with more moderate limitation. There will be a stepped approach to define ‘successful outcome’: baseline ARAT 0–7 must improve by 3 or more points; baseline ARAT 8–13 improve by 4 or more points; baseline ARAT 14–19 improve by 5 or more points; baseline ARAT 20–39 improve by 6 or more points. Analyses will be by intention-to-treat. Logistic regression will be used to compare the primary outcome (success) between the three randomisation groups at 3 and 6 months, adjusting for any imbalance in key covariates. The use of multilevel logistic models will be explored. It may be possible to fit three-level models (hubs, spokes and participants), but since there are only four centres with a hub, and a small number of stroke services accessing an InMotion robotic gym system at each hub, it may be necessary to fit a two-level model (stroke services and participants).

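### Staff may withdraw participants from the study, with no separation of stopping therapy from stopping follow-up, which puts the intention-to-treat comparisons at risk of bias

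*Protocol article*

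**What the plan says.** The Study withdrawal section opens with "No specific withdrawal criteria have been pre-set". It lets participants leave when they wish and adds "Data collected prior to withdrawal will be used in the study analysis unless consent for this is specifically withdrawn". A second paragraph extends the power to staff: "Investigators, GPs, stroke physicians and therapists may also withdraw participants from the study at any time". The ground given for such a decision is a judgement of welfare, namely "if they feel it is no longer in their interest to continue; for example, because of intercurrent illness or adverse events". Leaving the study is the only kind of exit described. Stopping trial therapy while remaining in follow-up is not mentioned.

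Four other sections bear on this:

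- Blinding: "it is not possible to blind participants or treating therapists to treatment allocation".
- Primary analysis: "The primary outcome is arm function measured by the ARAT [11] at 3 months", and "Analyses will be by intention-to-treat".
- Secondary analyses: differences in attrition and non-random attrition will be considered, the pattern of missing data will be examined, and multiple imputation will be considered if enough data are missing.
- Sample size: 240 per group are randomised so that 216 respond, an allowance of 10% for attrition.

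**The concern.** Stopping a therapy and stopping follow-up are different decisions. An intention-to-treat comparison can absorb the first, but it depends on the second being rare or unrelated to outcome. Here one clause covers both. A site that follows it as written could stop assessing someone whom a therapist or doctor has withdrawn, and no later analysis can recover an ARAT that was never measured.

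Three features make such losses potentially informative and unequal:

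- The triggers given as examples are health events, which may plausibly be related to arm recovery.
- The treating therapists know the allocation.
- Both therapy arms have 36 scheduled sessions over 12 weeks, nearly the whole period up to the primary endpoint. Usual care has no matching contact with study therapists.

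If participants with a poorer outlook leave the therapy arms more often than usual care, those who remain in the therapy arms look better than the randomised groups did.

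**Working it through.** **The plan's own figures.** 216 / (1 − 0.10) = 240 per group, and 3 × 240 = 720, as stated. The significance level is 0.05 / 3 = 1.67%. No reference success rate is given. The 216 is close to what an assumed 30% v 45% requires (217 per group, two-sided, no continuity correction). The attrition allowance restores the number of responders. It does nothing about which participants respond.

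**Inputs for the illustration.** From the Sample size section: 216 responders per group and a 1.67% level, taken as two-sided (critical value 2.393). Assumed, because the documents give no figure:

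- true success s = 40% in every arm, so there is no real difference;
- fraction withdrawn before 3 months w;
- success q that those withdrawn would have had;
- an analysis of observed outcomes only.

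**Formulas.** Observed success in an arm = (s − w·q) / (1 − w). Bias B is the difference between arms in observed success. SE = √(2 × 0.40 × 0.60 / 216) = 0.0471. Type I error = Φ(B/SE − 2.393) + Φ(−B/SE − 2.393).

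**Therapy arm v usual care, no withdrawal in usual care (observed 40%).**

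| w in therapy arm | q | Observed success | Bias (points) | Type I error |
|---|---|---|---|---|
| 5% | 0% | 0.40/0.95 = 42.1% | +2.1 | 2.8% |
| 5% | 20% | 0.39/0.95 = 41.1% | +1.1 | 1.9% |
| 5% | 40% | 0.38/0.95 = 40.0% | 0 | 1.67% |
| 10% | 0% | 0.40/0.90 = 44.4% | +4.4 | 7.4% |
| 10% | 20% | 0.38/0.90 = 42.2% | +2.2 | 2.9% |
| 10% | 40% | 0.36/0.90 = 40.0% | 0 | 1.67% |

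Worked row (10%, q = 0): B/SE = 0.0444/0.0471 = 0.943, so the error is Φ(−1.450) + Φ(−3.336) = 0.0735 + 0.0004 = 7.4%. Using 240 randomised less those withdrawn in place of a fixed 216 changes the two worst rows only slightly, to 2.9% and 7.6%.

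**Some withdrawal in usual care too (10% v 5%).** With q = 0 the bias is 44.4 − 42.1 = +2.3 points (3.1%). With q = 20% it is +1.2 points (2.0%). With q = 40% it is 0.

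**Equal withdrawal and the same prognosis (10% v 10%).** The bias is 0 and the error stays at 1.67%, whatever q is. On the contact argument alone this is the position for robot-assisted training v enhanced therapy, whose sessions are matched in frequency and duration.

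**Other base rates.** With q = 0 and no withdrawal in usual care, a true success of 30% to 50% gives +1.6 to +2.6 points at 5% withdrawal and +3.3 to +5.6 points at 10%.

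**The case against.** A good deal can be said for the plan.

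- The sentence on data collected before withdrawal says that such data are kept. It does not say that nothing further may be collected, and it stands in the paragraph on participants' own withdrawal. A reader might infer that follow-up is barred after withdrawal, but the text does not say so. What stands is that it makes no provision for follow-up either.
- A reader might infer that staff will remove those whose arm is recovering poorly. The examples are illness and adverse events, and no withdrawal rate, split by arm or prognosis is given. GPs and stroke physicians are also named, and they are not tied to the therapy arms. Unequal loss is therefore plausible but not shown.
- The Secondary analyses section addresses differential and informative attrition directly. This is real mitigation, but partial: it is conditional, it acts after the outcomes are lost, and standard multiple imputation assumes data missing at random.
- Analysing participants as randomised is distinct from having complete outcomes. The intention-to-treat label is not falsified by some attrition, which the sample size anticipates.
- The article condenses a full protocol that may separate the two events. The article nevertheless states a rule on who may withdraw participants and from what, and that rule is what is questioned here.

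**Conclusion.** The point holds as a risk created by the wording. It is not a demonstrated bias. The clause lets unblinded therapists, among others, end study participation without saying that outcomes will still be sought, so the 3-month ARAT may be lost for health-related reasons. The exposed comparisons are chiefly the two against usual care. For robot-assisted training v enhanced therapy the contact argument gives no bias if withdrawal and prognosis are equal in those arms.

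On the main assumptions (40% true success, no withdrawal in usual care, withdrawn participants doing no better than the rest) the bias is at most 2.1 points at 5% withdrawal and 4.4 points at 10%, against a target difference of 15 points. It can equally be zero. The upper ends require that nobody withdrawn would have succeeded.

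A stronger conclusion, that the comparison is biased or that intention-to-treat fails, would need withdrawal rates and prognosis by arm, which the documents do not contain. The wording should be amended, because the remedy is cheap and a missing outcome cannot be restored at analysis.

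**What to change.** Leave the clinicians' decision to stop participation in trial therapy as it is. Add that participants so withdrawn remain in outcome follow-up, and that the 3- and 6-month assessments are still sought unless the participant withdraws consent to follow-up or is unable to take part. Record end of therapy and end of follow-up as separate events, each with date, reason and who decided, and report both by arm.

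The cost is a change of protocol wording, a note to sites, and a few assessments that are already in the schedule. The sample size does not change. The Trial status section reports 468 recruited of the planned 720, so the change could cover at least the remaining 720 − 468 = 252 participants, counted from submission of the article.

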### Safety evaluation

The safety of robot-assisted training, enhanced upper limb therapy and usual care is being evaluated by examining the occurrence of all adverse events and serious adverse events in accordance with National Research Ethics Committee (NRES) guidance for non-CTIMP trials [36].

### Statistical analysis

#### Primary analysis

The primary outcome is arm function measured by the ARAT [11] at 3 months. It has been suggested that the minimal clinically important difference for the ARAT is 10% of its range (6 points) [37] but a smaller treatment effect may be clinically beneficial in those with severe initial upper limb functional limitation who are likely to improve less than those with more moderate limitation. There will be a stepped approach to define ‘successful outcome’: baseline ARAT 0–7 must improve by 3 or more points; baseline ARAT 8–13 improve by 4 or more points; baseline ARAT 14–19 improve by 5 or more points; baseline ARAT 20–39 improve by 6 or more points. Analyses will be by intention-to-treat. Logistic regression will be used to compare the primary outcome (success) between the three randomisation groups at 3 and 6 months, adjusting for any imbalance in key covariates. The use of multilevel logistic models will be explored. It may be possible to fit three-level models (hubs, spokes and participants), but since there are only four centres with a hub, and a small number of stroke services accessing an InMotion robotic gym system at each hub, it may be necessary to fit a two-level model (stroke services and participants).

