### Case ascertainment and recruitment

Study participants are recruited from both incident and prevalent stroke populations. Participants can be sought from a number of settings in both primary and secondary care including: stroke units; outpatient clinics; day hospitals; community rehabilitation services; and general practices. The study aims to recruit similar numbers of participants within: 0–3 months of stroke; >3–12 months after stroke; and >12 months to 5 years after stroke.

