### Randomisation

Randomisation is conducted by the local study coordinator/NIHR LCRN staff following completion of the baseline assessment. A central independent web-based service hosted by Newcastle University Clinical Trials Unit is used. Participants are stratified according to study centre, time since stroke and severity of upper limb function (ARAT score [11]), and randomised to either robot-assisted training, enhanced upper limb therapy, or usual care groups using permuted block sequences.

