#### Secondary analyses

The secondary outcomes will be compared between the three groups at 3 and 6 months using multilevel linear regression adjusting for baseline values and key covariates.

We will consider any difference in attrition rates, and any nonrandomness of the attrition, when comparing outcomes between the three groups. The pattern of missing observations because of loss to follow-up will be examined to determine both the extent of missingness, and whether it is missing at random or is informative. If data are missing to a sufficient extent, the use of appropriate multiple imputation techniques will be considered. Although mortality is possible within the 6-month follow-up period, it is thought to be sufficiently uncommon that methods for joint modelling of survival and longitudinal data will not be necessary.

Further descriptive analyses will explore the relationship between the severity of baseline upper limb function and time since stroke upon the effectiveness of the intervention. There is not sufficient power to perform any formal subgroup analyses. The time pattern of upper limb recovery will be explored by extending the earlier multilevel models to include a further within-patient level (ARAT scores collected at baseline, 3 and 6 months). However, this will depend on the relationship being approximately linear.

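### Covariate adjustment of the primary model hangs on observed imbalance, a trigger that would not normally select the stratification factors; fix those factors in the model in advance

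*Protocol article*

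**What the plan says.** Under Primary analysis, the article states: "Logistic regression will be used to compare the primary outcome (success) between the three randomisation groups at 3 and 6 months", followed by "adjusting for any imbalance in key covariates". It does not list the key covariates, and it names neither the stratification factors nor baseline ARAT as fixed terms. It adds: "The use of multilevel logistic models will be explored". The levels mentioned are hubs, spokes and participants, or stroke services and participants.

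Under Randomisation: "Participants are stratified according to study centre, time since stroke and severity of upper limb function", "using permuted block sequences".

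Under Secondary analyses, the rule is different: "multilevel linear regression adjusting for baseline values and key covariates", with no reference to imbalance.

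Two other places bear on how prognostic the factors may be. Case ascertainment and recruitment says "The study aims to recruit similar numbers of participants within" three time bands running from the first 3 months to 5 years after stroke. Primary analysis explains its stepped definition of success by pointing to severely limited patients, "who are likely to improve less than those with more moderate limitation".

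**The concern.** The wording makes adjustment conditional on what the baseline table shows. Stratified permuted blocks are there to keep centre, time since stroke and severity band similar across groups, so a rule that looks for imbalance will usually pass over them. Yet a stratified design calls for these variables in the analysis. Stratification removes between-stratum variation from the treatment comparison, and a model that ignores the strata still counts that variation in its standard error.

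At stake is efficiency and correct calibration of the primary test. Intervals would be wider than the design warrants, and power the design has already paid for would go unused. The primary outcome would also be analysed under a weaker rule than the secondary outcomes.

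**Working it through.** **1. The plan's own figure.** Inputs from Sample size: 216 evaluable per group, 80% power, significance level 1.67%, difference 15 points, 10% attrition. The test is taken as two-sided. The comparator success rate is not given.

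n = [z(α/2)·√(2p̄(1−p̄)) + z(β)·√(p₁(1−p₁) + p₂(1−p₂))]² / 0.15², with z(α/2) = 2.393 and z(β) = 0.842.

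- At 29.5% against 44.5%: p̄ = 0.37, and n = (2.393 × 0.6828 + 0.842 × 0.6745)² / 0.0225 = 215.5, so 216.
- At 30% against 45%: 217, with power 79.9% at 216.
- Over comparator rates of 20-50% the formula gives 185-232 per group, and power at 216 runs from 86.7% down to 76.8%.
- 216/0.9 = 240, and 3 × 240 = 720.

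The stated size reproduces with a comparator rate near 30%.

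**2. What omitting a prognostic stratifier does to the test.** Assumptions: two arms of 216, three equal time-since-stroke strata (72 per arm per stratum), and the comparator success rates below. None of these rates is in the article. Under the null, with the strata balanced, the true variance of the difference depends on the mean of p(1−p) within strata (W). The unadjusted model uses p̄(1−p̄) overall (T). The true SE is √(W/T) times the reported one, so the effective critical value is 2.393/√(W/T).

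| Stratum success rates | W | T | √(W/T) | Effective critical value | Type I error |
|---|---|---|---|---|---|
| 45/35/25% | 0.2208 | 0.2275 | 0.985 | 2.429 | 1.5% |
| 60/35/20% | 0.2092 | 0.2364 | 0.941 | 2.544 | 1.1% |
| 70/35/15% | 0.1883 | 0.2400 | 0.886 | 2.702 | 0.7% |
| No difference between strata | W = T | | 1 | 2.393 | 1.67% |

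**3. Simulation of the same cases.** 200,000 replicates, pooled two-proportion test against a Mantel-Haenszel test, with a common odds ratio set to give a 15-point marginal difference:

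| Stratum success rates | Type I error, unadjusted | Power, unadjusted | Power, stratified | Forgone |
|---|---|---|---|---|
| 45/35/25% | 1.54% | 78.7% | 79.2% | 0.5 points |
| 60/35/20% | 1.06% | 79.5% | 82.8% | 3.3 points |
| 70/35/15% | 0.70% | 80.7% | 87.1% | 6.4 points |

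The simulated type I errors match the formula.

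**4. All three factors together.** A separate simulation fitted the logistic model with and without the stratum main effects. It assumed 48 strata (4 centres × 3 time bands × 4 ARAT bands), permuted blocks of 4, and 30% against 45% success. Prognostic strength is the standard deviation (SD) of the stratum effects on the logit scale.

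| Logit SD | Power, omitted | Power, adjusted | Type I error, omitted |
|---|---|---|---|
| 0 | 79.0% | 79.4% | about nominal |
| 0.5 | 79.8% | 82.4% | 1.2-1.5% |
| 1.0 | 81.4% | 87.5% | 0.9-1.1% |
| 1.5 | 83.6% | 93.2% | 0.4-0.5% |

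The last row, a gap of about 10 points, assumes very strong prognosis and is shown as an outer bound. With the factors in the model and prognostic, type I error was about 1.6-1.8%.

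**5. Does the multilevel option close the gap?** It could carry centre or service, but not time since stroke or severity. With centre alone in the model, type I error was 1.5%, 1.2% and 0.7% at SD 0.5, 1.0 and 1.5, so the correction is only partial.

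**The case against.** The strongest reply is that nothing in the article excludes the stratification factors. The key covariates are unnamed, a list of them commonly belongs in an analysis plan, and that plan is not shown. Centre has a possible route in through the multilevel models. Baseline ARAT as a score can still be imbalanced within severity bands and so be picked up. The stepped success thresholds are meant to weaken the link between baseline ARAT and success. All of this stands, and it limits the point to what the stated rule would normally do. It does not remove the point: the article states a trigger rather than leaving the matter open, and an analysis plan would have to depart from that wording to put it right. The thresholds also do nothing about time since stroke.

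A reader might infer more than the article supports:

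- That the primary result would be invalid or the trial underpowered. The error is conservative, and the unadjusted analysis keeps roughly the planned 80% (78.7-80.7% in step 3, 79-84% in step 4). The loss is only relative to an adjusted model.
- That choosing covariates by imbalance lets outcome knowledge shape an open-label trial's estimate. Baseline balance can be judged without outcome data, the face-to-face assessors are intended to be blinded, and only the data monitoring committee sees unblinded outcomes before the end.
- That an odds ratio is an error because the target is a difference in proportions. Sizing on one scale and testing by logistic regression is routine, and the article does not say that odds ratios alone will be reported.

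**Conclusion.** The point holds, at moderate severity. As worded, the rule would not normally bring centre, time since stroke and severity into the primary model, and it is weaker than the rule for the secondary outcomes. If those factors predict success, standard errors are too large: under the three assumed patterns in steps 2 and 3, type I error is about 0.7-1.5% instead of 1.67%, and roughly 1 to 6 points of power are forgone. These sizes rest on assumed stratum success rates, equal strata and a two-sided test. The article gives no figure for prognostic strength, and with none there is no loss. The sample size of 720 needs no change.

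**What to change.** Replace the imbalance phrase with one pre-specified primary model: logistic regression of 3-month success on randomised group, study centre, time since stroke (randomisation categories) and baseline ARAT, fitted whatever the observed balance. Any further key covariates should be named in advance. If a multilevel model is used for centre or service, time since stroke and baseline ARAT stay in as fixed terms.

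The cost is one sentence in the protocol or analysis plan. All the variables are already collected for eligibility and randomisation, and the sample size is unchanged. A standardised risk difference with its confidence interval beside the odds ratio would put the result on the scale of the 15-point target; that is an optional addition, not a correction.

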**Methods/design:**

Study design: a pragmatic, three-arm, multicentre randomised controlled trial, economic analysis and process evaluation.

Setting*:* NHS stroke services.

Participants: adults with acute or chronic first-ever stroke (1 week to 5 years post stroke) causing moderate to severe upper limb functional limitation.

Randomisation groups:

1. Robot-assisted training using the InMotion robotic gym system for 45 min, three times/week for 12 weeks

2. Enhanced upper limb therapy for 45 min, three times/week for 12 weeks

3. Usual NHS care in accordance with local clinical practice

Randomisation: individual participant randomisation stratified by centre, time since stroke, and severity of upper limb impairment.

Primary outcome: upper limb function measured by the Action Research Arm Test (ARAT) at 3 months post randomisation.

Secondary outcomes: upper limb impairment (Fugl-Meyer Test), activities of daily living (Barthel ADL Index), quality of life (Stroke Impact Scale, EQ-5D-5L), resource use, cost per quality-adjusted life year and adverse events, at 3 and 6 months.

Blinding: outcomes are undertaken by blinded assessors.

Economic analysis: micro-costing and economic evaluation of interventions compared to usual NHS care. A within-trial analysis, with an economic model will be used to extrapolate longer-term costs and outcomes.

Process evaluation: semi-structured interviews with participants and professionals to seek their views and experiences of the rehabilitation that they have received or provided, and factors affecting the implementation of the trial.

Sample size: allowing for 10% attrition, 720 participants provide 80% power to detect a 15% difference in successful outcome between each of the treatment pairs. Successful outcome definition: baseline ARAT 0–7 must improve by 3 or more points; baseline ARAT 8–13 improve by 4 or more points; baseline ARAT 14–19 improve by 5 or more points; baseline ARAT 20–39 improve by 6 or more points.

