### Study setting

The study is being conducted in NHS stroke units in the UK. There are four RATULS study centres (Glasgow, North Tyneside, Northwick Park, and Romford) each consisting of a hub site with an InMotion robotic gym system and spoke sites which are stroke services in adjacent trusts that refer patients to take part in the study and provide usual NHS care.

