### Randomisation groups

#### Robot-assisted training using the InMotion robotic gym system

This is delivered using the InMotion robotic gym system which was specifically designed for clinical rehabilitation applications [23–25]. This is currently the most widely used technology for robot-assisted training for patients with moderate to severe upper limb impairment post stroke. The system development started in 1989 and it has amassed the largest body of clinical evidence to date of any robotic system. It has been successfully tested in clinical studies involving over 900 stroke patients and there are around 250 robots in use worldwide.

Participants receive robot-assisted training at the hub sites for up to 45 min per day, three days per week for 12 weeks, in addition to usual care. A detailed description of the robot-assisted training programme using the Template for Intervention Description and Replication (TIDieR) Checklist [26] is provided in Table 1.

**Table 1 Tab1:** Template for Intervention Description and Replication (TIDieR) Checklist for the RATULS trial intervention treatments

Item	Intervention group	
1. Brief name: *‘provide the name or phrase that describes the intervention’*	*Robot-assisted training*	*Enhanced upper limb therapy*

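### Study centre is a randomisation stratum, but the stated adjustment rule does not guarantee it a place in the primary model

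*Protocol article*

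**What the plan says.** The abstract of the Protocol article describes "individual participant randomisation stratified by centre, time since stroke, and severity of upper limb impairment", and the Randomisation section confirms centre as a stratum, with permuted blocks. Study setting gives the number: "There are four RATULS study centres", each made up of a hub and referring spoke services.

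Delivery is described by arm. "Participants receive robot-assisted training at the hub sites", and likewise "Participants receive enhanced upper limb therapy at the hub sites". For the third arm, "Usual care is delivered at hub and spoke sites".

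The Primary analysis section commits to logistic regression for success, with adjustment made for any imbalance found in key covariates. The covariates are not listed. It then adds: "The use of multilevel logistic models will be explored". A three-level model (hubs, spokes, participants) is described as perhaps possible. Because there are only four hubs and few services at each, "it may be necessary to fit a two-level model (stroke services and participants". Fixed effects for centre are not mentioned.

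**The concern.** A factor used to stratify the randomisation is normally carried into the analysis. Here nothing in the text ensures that.

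- **The covariate rule works against it.** Adjustment is triggered by observed imbalance. Blocked randomisation within centre is designed to prevent imbalance by centre. A rule of this kind will therefore tend to pass over centre, even though the case for including it is that it predicts outcome and was used in the design.
- **The multilevel route does not settle it either.** Of the two structures named, one estimates a hub variance from four units and the other contains no hub level. Both are only to be explored.

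What is at stake is efficiency. If hubs differ in success rate and the model ignores this, the model-based standard error does not reflect the precision gained by stratifying. The log odds ratio is also drawn towards zero, because odds ratios averaged over unlike centres are smaller than those within centres. The result is a conservative test and some loss of power, not false positives.

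**Working it through.** **Inputs from the Protocol article.** Four centres; 216 evaluable participants per arm; significance level 1.67%; 10% attrition; a 15-point difference in success.

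**The plan's own figures.** 5%/3 = 1.67%. 216/(1 − 0.10) = 240 per group, 720 in total. The 216 needs a reference success rate, which the article does not give. With a two-sided pooled two-proportion formula, 30% v 45% gives 217 per arm, and 42.5% v 57.5% gives 232 (power 76.8% with 216). The article's sample size is therefore consistent with some reference rates but cannot be derived uniquely.

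**Cost of fixed centre effects.** 4 − 1 = 3 parameters, among 3 × 216 = 648 analysed participants.

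**A variance from four hubs.** On 3 degrees of freedom, the normal-theory 95% interval for the between-hub SD runs from √(3/9.348) = 0.57 to √(3/0.216) = 3.73 times its estimate. This is only indicative for a logistic model, and the hub SD is a nuisance parameter, so the effect on the treatment comparison has to be checked directly.

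**Direct check by simulation.** These inputs are assumed, not taken from the article: 5 services per hub, equal hubs with 54 participants per arm (4 × 54 = 216), success 42.5% v 57.5% (log odds ratio 0.60), service SD 0.2 on the logit scale, and 400 replicates per setting. Monte Carlo error is √(0.0167 × 0.9833/400) ≈ 0.6 points for type I error and about 2.3 points for power. To give the hub SD a meaning: logit(42.5%) = −0.30, so hubs one SD below and above have control success of 35% and 50% (SD 0.3), 29% and 57% (SD 0.6), or 21% and 67% (SD 1.0).

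| Hub SD | Quantity | No centre term | Service random intercept | Hub + service random | Fixed centre |
|---|---|---|---|---|---|
| 0.3 | Power | 74% | 74% | 74% | 74% |
| 0.6 | Power | 71% | 72% | 73% | 73% |
| 1.0 | Power | 59% | 67% | 67% | 67% |
| 0.3 | Type I error | 1.8% | 2.0% | 1.8% | 1.8% |
| 0.6 | Type I error | 1.0% | 1.3% | 1.3% | 1.3% |
| 1.0 | Type I error | 0.5% | 0.5% | 1.0% | 1.3% |

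The columns should be compared within a row. The fall in the fixed-centre column from 74% to 67% comes from hubs with extreme success rates, not from the choice of model.

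**Why omission costs power at SD 1.0.**
- Under no effect, the model without centre reports a mean standard error of 0.1994, while its estimates vary with SD 0.1871. The standard error is too large by a factor of 0.1994/0.1871 = 1.07. With fixed centre the two agree (0.2153 and 0.2143).
- Under the assumed effect, the mean log odds ratio shrinks from 0.61 to 0.52. The ratio of mean estimate to mean standard error is 0.523/0.1993 = 2.62 without centre and 0.608/0.2164 = 2.81 with it.

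A separate simulation under assumed inputs agrees at SD 1.0: power 60% v 67% and type I error 1.1% v 1.6%, without and with fixed centre. It shows no difference at 0.3.

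**The two multilevel options.** At SD 0.6 under the assumed effect, the mean standard error is 0.2035 with the service intercept and 0.2040 with fixed centre. In the three-level model the hub variance was estimated at about zero in 26% of replicates at SD 0.3, 4–6% at 0.6 and about 1% at 1.0. That is, it collapses mostly where hub differences hardly matter.

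**The case against.** The strongest reply is that the text does not fix a faulty model. Several parts of it stand.

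- A reader might infer that the primary model must be either the three-level or the hub-free two-level one. The section does not say so: logistic regression is the committed analysis and both structures are hedged. The authors raise the four-hub difficulty themselves.
- A reader might infer that the two-level model discards centre and is therefore invalid. Services are nested within centres, so a service intercept absorbs most hub differences, and nothing bars centre as a covariate alongside it. Nor is service an irrelevant level: usual care is given at spokes as well as hubs, and all three arms receive it. In the simulation neither structure inflated type I error beyond Monte Carlo error, and power was within about a point of fixed centre.
- A reader might infer that the level structure will be chosen after looking at outcomes. The reason given is the number of hubs and services, which can be counted without outcome data.
- The full analysis plan is not shown and may name centre as a covariate.

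This does not remove the narrower point. The article does state a covariate rule for the primary test, and that rule depends on imbalance. Applied as written, it gives a balanced stratification factor no assured place, and the committed logistic model may then contain no centre term at all.

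**Conclusion.** The point holds as a weakness in how the primary model is specified: a four-level stratification factor is left to an imbalance rule, or to multilevel models that are only to be explored. It does not show that the named multilevel models are wrong, or that the trial risks extra false positives. If centre is omitted, the error is on the conservative side.

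The size depends on how much hubs differ. There is no loss at a between-hub SD of 0.3, about 2 points of power at 0.6 (within simulation error), and about 7 points at 1.0, from about 67% to about 60%. An SD of 1.0 is a large spread between hubs, so small to moderate is a fair expectation. These figures rest on assumed success rates, equal hubs, five services per hub and a service SD of 0.2. None of these is in the article.

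Delivery of both therapies at the hubs raises a separate question, whether treatment effects differ by hub. Fixed centre intercepts do not answer it.

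**What to change.** In the Primary analysis section, or in the analysis plan if it does not already say so, state that study centre enters the primary logistic model as a four-level fixed effect, whatever the observed balance. State the same for the secondary models. A random intercept for stroke service within centre may be added as a sensitivity analysis.

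The change is one of wording. It uses 3 parameters among about 648 analysed participants, needs no hub variance to be estimated, and requires no further data or participants.
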